#### Secondary

Secondary outcomes include: (1) to understand the perceptions and barriers of caregivers regarding immunization and (2) to understand the perception of caregivers related to personalized mobile phone–based SMS text messages and automated health messages for vaccination improvement.

### Methodology

#### Study Design

The study design is a mixed method clustered randomized controlled trial (RCT) augmented by qualitative interviews (Figure 1). The cluster trial will be used to assess the respective impacts of mobile phone and SMS-based communications on RI coverage rates among children at 20 weeks of age. Initially, structured interviews will be conducted at baseline to identify barriers to immunization and role of SMS and automated call–based messages in improving vaccination coverage. This information will lead to the development of personalized barrier-specific messages (SMS and voice calls) that will be used for each participant or caregiver according to the specific barriers they struggle with, as identified at baseline.

#### Study Sites

The Department of Paediatrics and Child Health at the Aga Khan University (AKU) conducts active health demographic surveillance systems (HDSS) at several urban sites in Karachi. These sites are (1) Ibrahim Hydri Goth, (2) Ali Akber Shah Goth, (3) Rehri Goth, and (4) Bhains colony, which is part of Bin Qasim Town (Figure 2). Ibrahim Haidry Goth, Ali Akber Shah Goth, and Rehri Goth are located along the sea coast of Karachi, and the main occupation of people living in these communities is fishing. Bhains Colony is located at the outskirts of Karachi, and the main source of income of its population is dairy products.

**Figure 1 figure1:**
[figure not shown]
Study design: a mixed methods randomized controlled trial (RCT) augmented by qualitative interviews. SMS: short message service.

**Figure 2 figure2:**
[figure not shown]
Catchment area of Karachi pre-urban demographic surveillance site.

The HDSS sites are divided into 195 blocks, each containing 250 structures and mapped using the geographical information system. There are a total of 42,093 structures where 43,098 households are living in areas of Korangi and Bin Qasim towns [19]. A *structure* is defined as a building with a single entrance and a boundary. These structures can be houses, hospitals, dispensaries, schools, shops, parks, etc. Each structure has a unique number assigned to it. The total population of the active surveillance catchment area is approximately 0.3 million, with around 7115 pregnant women and 6831 NBs being followed annually by the surveillance team. Within 1 block, the 250 administrative structures will be our trial clusters; 4 sites will be participating in the study. NBs will be enrolled from the HDSS, and clusters within the 4 sites will be randomly assigned to the study arms. Hence, participants within each administrative structure (ie, cluster) will receive same intervention.

Data will also be collected from the rural site of Matiari, which is located in Sindh province 185 km north of Karachi (Figure 3). The department of pediatrics will partner with the local Lady Health Worker (LHW) program Sindh. Information about new births within LHW catchment area will be provided to the study team. The catchment areas in Matiari are the areas covered by each LHW; these areas are small and that is why the catchment area of 4 LHWs will be considered as 1 cluster. The total population of the Matiari District area is approximately 0.4 million. A total of 3 main sites from district Matiari will be the part of study, which includes Matiari, Hala, and Saeedabad. The main source of income in this area is agriculture. In Matiari and Karachi, clusters will have a mean of 15 births per cluster.

**Figure 3 figure3:**
[figure not shown]
The Matiari site: catchment area of surveillance site.

#### Baseline Survey

A total of 50 interviews will be conducted from Karachi and Matiari sites (ie, 25 interviews from each site). From the HDSS, list of caregivers who have completed the vaccination schedule and those who are dropouts or not vaccinating their child was taken out, and randomly, caregivers will be selected for in-depth interviews. Trained staff will conduct the qualitative interviews. Depending upon the availability, caregivers will be approached at the household, and appointments will be taken from the caregiver so that they can spare enough time for the discussion. Through in-depth interviews, we will explore the perceptions and barriers related to EPI and mobile health from the caregivers. Information collected before the study through qualitative in-depth interviews will help in developing the survey to assess the different categories of barriers. The baseline survey will, overall, collect information on demographics, mobile phone access and usage, possible barriers for RIs, and factors associated with mobile phone–based health messages.

#### Qualitative Phase

##### Assessing Perceptions and Experiences of Caregivers About the Routine Immunization and the Role of Mobile Phone Short Message Service and Automated Calls in Improving the Routine Immunization Coverage and to Develop Messages

Initially, in-depth interviews with a subpopulation in the study catchment area will be conducted to explore RI immunization coverage among Pakistani caregivers and families to assess (1) perceptions regarding risks of infectious diseases preventable by vaccines and vaccine safety and efficacy, (2) barriers to vaccinating children including difficulties in visiting RI centers, and (3) perceptions and barriers that may affect mobile phone–based interventions to improve immunization coverage. The interviews will be conducted across the site regions. We will use purposive sampling to assure that participants represent different ethnic groups. Information gathered through the interviews will help in (1) understanding the types of barriers perceived by caregivers, (2) designing the RCT and, (3) developing content for SMS text messages in several categories of barriers. We expect 20 to 25 parents or caregivers to be interviewed over a period of 3 months, but the number will be guided by saturation of information. Each interview will take 45 to 60 min.

### Randomized Clinical Trial

The study design is a cluster randomized clinical trial including 4 intervention and 1 control arm (Table 2).

#### Sample Size Calculations

Assumptions used for calculating sample size are as follows: increase in coverage rate from 30% to 40%, having a power of 80% with an alpha error at .05. The sample size per arm would be 615 per arm or 3075 for all 5 arms. Adding a 10% dropout will make it 677 per arm or 3385 recruitment for all 5 study arms. The ICC is taken as .05, with an estimate of 15 NB per cluster (see Table 3).

**Table 2 table2:** Cluster randomized clinical trial.

Study arm	Automated SMS^a^ text and phone calls			
	1-way SMS text	2-way SMS text	1-way phone calls	2-way phone calls
1	X^b^	—^c^	—	—
2	—	—	X	—
3	—	X	—	—
4	—	—	—	X
5	—	—	—	—

^a^SMS: short message service.

^b^Applicable.

^c^Not applicable.

**Table 3 table3:** Sample size calculation. Having a difference of 10% and the sample size given (ie, 1230 is 2 groups, 1:1) in our study, we have 5 groups (615x5)+10% dropout=3385.

Serial #	Interclass correlation	Range of cluster size					
		Cluster size of 15		Cluster size of 20		Cluster size of 30	
		Clusters, n	Total birth required, n	Clusters, n	Total birth required, n	Clusters, n	Total birth required, n
1	0.01	54	810	44	880	32	960
2	0.05	82	1230	70	1400	58	1740
3	0.09	108	1620	98	1960	86	2580
4	0.1	114	1710	104	2080	94	2820
5	0.13	134	2010	124	2480	114	3420
6	0.15	148	2220	138	2760	128	3840
7	0.2	180	2700	172	3440	162	4860
8	0.21	188	2820	178	3560	168	5040
9	0.25	214	3210	206	4120	196	5880
10	0.3	248	3720	238	4760	230	6900
11	0.35	280	4200	272	5440	264	7920
12	0.37	294	4410	286	5720	278	8340
13	0.4	314	4710	306	6120	300	9000
14	0.45	346	5190	340	6800	334	10,020
15	0.5	380	5700	374	7480	368	11,040

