### Statistical Analysis

Analyses will be conducted according to the intention-to-treat principle. When the information cannot be gathered, the vaccine status of the child will be *failure* (conservative approach). Missing the vaccine EPI card to verify vaccine status at home will lead to a deeper investigation in the family and also the vaccine clinic. From previous experience, we expect this process to be successful in identifying the outcome of over 95% (95/100) of the children who remain in the study at 20 weeks. Families that have left the study for any reason (moving, withdrawal, child death) will be interviewed (if possible) and the information gathered used for the outcome classification. If the information is not clear or incomplete, the child’s status regarding vaccination will be *failure*.

The main analyses will be comparing our 4 study intervention arms against the control, and with each other. For the purposes of our study, we will compare each of the 4 interventions with each other and with the control arm. For example, 1-way versus 2 SMS, reminder versus educational SMS, 1-way reminders SMS versus control, 1-way educational SMS versus control, 2-way reminders SMS versus control, 2-way educational SMS versus control, 2-way education versus 1-way reminder, and 2-way reminder versus 1-way educational.

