### Analysis of Quantitative Data

Analyses will be conducted according to the intention-to-treat principle, and the Bonferroni correction will be used to control for multiple testing. The primary outcome is to assess difference in vaccination status. Chi-square test will first be used to compare the groups’ percentage. Multivariable logistic regression analyses will be conducted to adjust for confounders. As our randomization unit is cluster-based rather than individual-based, generalized linear mixed effects models or generalized estimating equations models will be employed to account for within-cluster correlation, and hierarchal models will be used. The statistical model for the primary and secondary analyses will be developed as explanatory variables. As secondary analyses of the primary outcome, time-to-immunization curves will be constructed using the Kaplan-Meier method and Cox regression for multivariate analysis.

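### The sample size holds for one unadjusted two-arm comparison, but the planned Bonferroni correction is ignored: power for a 10-point difference falls from about 80% to about 63% (4 tests) or 51% (10 pairs)

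*Protocol article*

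**What the plan says.** Under Sample Size Calculations, the protocol article assumes an "increase in coverage rate from 30% to 40%, having a power of 80% with an alpha error at .05". It adds that "The ICC is taken as .05, with an estimate of 15 NB per cluster", and concludes: "The sample size per arm would be 615 per arm or 3075 for all 5 arms". The caption of Table 3 shows the basis: 1230 is the total for two groups at 1:1, and half of that is multiplied by five arms before 10% is added for dropout (3385 in all).

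Under Statistical Analysis, the main analyses are described differently: "we will compare each of the 4 interventions with each other and with the control arm". Under Analysis of Quantitative Data, "the Bonferroni correction will be used to control for multiple testing". Neither section gives the number of tests or the corrected alpha.

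**The concern.** The alpha in the sample size is not the alpha at which the planned tests will be run. Four comparisons with control plus six among the interventions make ten pairs of arms. Under Bonferroni no member of that family is tested at .05, yet the only power statement in the article is made at .05.

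The 10-point gain is the trial's own target, both in the sample size and in the first two primary outcomes. If a given arm truly achieves it, a reader of the protocol expects it to be missed about 20% of the time. Under the planned correction the miss rate is about 37% (4 tests) to 49% (10 pairs). A non-significant arm could then be read as an arm without a worthwhile benefit, on the strength of a power figure that does not apply to that test.

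**Working it through.** **Inputs.** From Sample Size Calculations and Table 3: 30% versus 40%, alpha .05, power 80%, ICC .05, 15 per cluster, 615 per arm, 677 with dropout. From Statistical Analysis: 4 + 6 = 10 pairs (my count). Assumption: the test is two-sided. The article does not say so, but a one-sided test gives only about 478 per arm, which does not match.

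**Reproducing the plan's figure.**
- Design effect = 1 + (15 − 1) × .05 = 1.70.
- n per arm before clustering = (1.960 + 0.842)² × (.21 + .24) / .10² = 353 (356 with pooled variance under the null).
- × 1.70 = 600 (605 pooled); / 15 = 40.0 (40.3), which exceeds 40 in both cases and rounds up to 41 clusters.
- 41 × 15 = **615 per arm**, or 82 clusters and 1230 for two groups. This matches Table 3 exactly.

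**Power at the corrected alpha, 615 per arm.**
- SE of the difference = √(1.70 × .45 / 615) = .0353, and .10 / SE = 2.835.
- Power = Φ(2.835 − z), where z is the two-sided critical value.

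| Bonferroni family | alpha per test | z | Power |
|---|---|---|---|
| 1 test (no correction) | .05 | 1.960 | 81% |
| 4 tests (each arm vs control) | .0125 | 2.498 | 63% |
| 10 tests (all pairs) | .005 | 2.807 | 51% |

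The method matters little. Pooled variance gives 80.6%, 62.7% and 50.5%. A t test on 80 degrees of freedom (82 clusters less 2) gives 80.0%, 61.1% and 48.4%.

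**Detectable difference at 80% power.** Solve d = (z + 0.842) × √(1.70 × [.21 + p(1 − p)] / 615) with p = .30 + d:
- alpha .05: d = 9.9 points
- alpha .0125: d = 11.8 points
- alpha .005: d = 12.9 points

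**Size needed to keep 80% power for 10 points**, from (z + 0.842)² × .45 / .01 × 1.70, before rounding to whole clusters and before dropout:
- 4 tests: about 853 per arm (861 with pooled variance)
- 10 tests: about 1018 per arm (1029 with pooled variance)

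**Does the dropout margin cover the gap?** No. If all 677 per arm had a known outcome, SE = √(1.70 × .45 / 677) = .0336 and .10 / SE = 2.975. Power is then 68% (4 tests) or 57% (10 tests). The Statistical Analysis section counts unresolved outcomes as failures. If, as an assumption, 10% in each arm were so counted, the rates become 27% and 36%, SE = √(1.70 × .4275 / 677) = .0328, and .09 / SE = 2.747. Power is then about 60% or 48%.

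**The case against.** **The stated figure is not wrong.** A reader might infer a calculation error. There is none: 80% and 615 follow from their stated inputs, and Table 3 openly labels the calculation as a two-group one. This objection stands. The fault is a mismatch between the sample size section and the analysis sections.

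**Power of 51% is one scenario, not a fact about the trial.** It needs a divisor of ten, which the article never states. It also needs a 10-point difference between interventions, whereas the primary outcomes attach the 10% increase only to comparison with standard care and give no effect size for one intervention against another. This also stands, so the result has to be given by family. It does not remove the point, because even the four comparisons to which the 10 points clearly apply have about 63% power. Nor is 51% a floor. The examples under Statistical Analysis add reminder-versus-educational contrasts, and five primary outcomes are listed, so the family could be larger than ten.

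**The divisor can be left to an analysis plan that is not shown.** True of the divisor. But the article itself fixes both the correction and the power claim, and no divisor of four or more makes the two agree.

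**The pooled questions are in the plan.** A reader might go further and say that messaging of any kind versus control, and SMS versus calls, have been left out. They have not: the first is in the abstract's objective and in primary outcome 1, and the second is in the third primary objective and primary outcome 5. A condensed article may leave out how they will be modelled.

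**Bonferroni still protects the type I error.** It does, so positive findings are not undermined. What is affected is the reading of negative ones.

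**Conclusion.** The point holds as an inconsistency. The trial was sized for a single two-arm test at alpha .05, while its main comparisons are to be run under a Bonferroni correction that the calculation ignores. For a 10-point difference at 615 per arm, power is about 63% if the family is the four comparisons with control. It is about 51% if the family is all ten pairs and 10 points is assumed between interventions too. The corresponding detectable differences are about 11.8 and 12.9 points, against 9.9 without correction.

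These figures rest on two-sided tests, the protocol's own 30% versus 40%, ICC .05 and 15 per cluster, and a normal approximation. The documents do not support calling the 615 or the 80% miscalculated, or quoting 51% as the trial's actual power.

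**What to change.** Keep the sample; enrolment was complete by January 2019. Before the analysis:

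1. State which comparisons form the Bonferroni family and what the divisor is.
2. Restate power and detectable difference under Sample Size Calculations at that alpha. For a family of four, for example: *615 per arm gives 81% power for one unadjusted comparison; with Bonferroni correction for the four comparisons with control (alpha .0125), power for 30% versus 40% is about 63%, and the difference detectable with 80% power is about 11.8 points.*
3. If comparisons between interventions are in the family, also state the difference assumed for them.

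The cost is wording and a less favourable stated power. No further participants are needed.

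Replacing Bonferroni with a fixed order that starts from pooled contrasts is optional and not part of this correction. It has a price. Treating the remaining pairwise tests as exploratory would demote primary outcomes 3 and 4, which ask about 1-way versus 2-way within SMS and within calls. A pooled first test can also be weak. If calls reach 40% and SMS stays at 30%, the pooled difference is 35% versus 30%, SE = √(1.70 × [.21/615 + .225/2460]) = .0271, and .05 / SE = 1.84. Power at .05 is then only about 45%.

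### The 10% dropout allowance assumes lost children leave the denominator, but the analysis keeps them in as failures; at 677 per arm, power is about 78% if the full 10% stay unresolved

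*Protocol article*

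**What the plan says.** Under Sample Size Calculations, the protocol article plans for a rise in coverage from 30% to 40%, "having a power of 80% with an alpha error at .05". On clustering it says: "The ICC is taken as .05, with an estimate of 15 NB per cluster". The result before loss is: "The sample size per arm would be 615 per arm or 3075 for all 5 arms". The allowance for loss follows: "Adding a 10% dropout will make it 677 per arm or 3385 recruitment for all 5 study arms". The Table 3 caption repeats it: "we have 5 groups (615x5)+10% dropout=3385".

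Under Statistical Analysis, the article specifies intention-to-treat and a rule for unknown outcomes: "When the information cannot be gathered, the vaccine status of the child will be" a failure. Families who leave through moving, withdrawal or child death are to be interviewed where possible and classified on what is learned. Failure applies to them only if that information is unclear or incomplete. For children who remain at 20 weeks, the article expects to establish the outcome in more than 95%.

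**The concern.** The two sections treat a lost child differently. The sample size adds children to replace those lost, which makes sense if lost children drop out of the analysis. The analysis drops nobody: a child whose status cannot be established stays in the denominator as unvaccinated. Under that rule, an unresolved share d multiplies both coverage rates by (1 − d). With d = 10%, a 10-point difference becomes 9 points. Adding children offsets some of the lost power but does not restore the difference, and the sample size is never worked out on the diluted rates.

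There is also a formula slip. Adding 10% to 615 does not leave 615 after 10% are lost; that requires dividing by 0.90.

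The recruitment target of 3385 and the 80% power claim both pass through this step.

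**Working it through.** **Inputs (Sample Size Calculations and Table 3).** Rates 30% and 40%; alpha .05, with sidedness not stated (two-sided reproduces the printed figure); power 80%; ICC .05; 15 newborns per cluster; equal allocation, since Table 3 describes its total as "1230 is 2 groups, 1:1".

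**1. Reproducing 615.** The two-proportion formula is n = [1.960·√(2p̄(1−p̄)) + 0.842·√(p₁(1−p₁) + p₂(1−p₂))]² / (p₂−p₁)². With p̄ = 0.35:
- n = (1.322 + 0.565)² / 0.01 = 356 per arm
- design effect = 1 + 14 × 0.05 = 1.70
- 356 × 1.70 = 605.2, or 40.3 clusters of 15; rounded up, 41 clusters = 615, as printed

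**2. Reproducing 677.** 615 × 1.10 = 676.5, rounded up to 677; × 5 = 3385, as printed.

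**3. The formula slip alone (lost children removed).**
- needed to retain 615: 615/0.90 = 683.3, so 684 per arm and 3420 in total; the gap is 684 − 677 = 7 per arm, or 1.0%
- retained from 677: 677 × 0.90 = 609.3, below 615 but above the unrounded 605.2
- power at 609.3 is 80.3%, against 80.6% at 615

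**4. Power under the failure rule.** Nobody leaves the denominator, so N = 677 and the effective size is 677/1.70 = 398.2. The rates become 0.30(1−d) and 0.40(1−d), with d taken as equal in both arms. Power = Φ{[(p₂−p₁)·√398.2 − 1.960·√(2p̄(1−p̄))] / √(p₁(1−p₁) + p₂(1−p₂))}. For d = 10%: (0.09 × 19.955 − 1.288)/0.654 = 0.778, and Φ(0.778) = 78.2%.

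| Unresolved share d | Rates | Difference | Power at 677 per arm |
|---|---|---|---|
| 0% | 30.0% vs 40.0% | 10.0 points | 84.2% |
| 5% | 28.5% vs 38.0% | 9.5 points | 81.3% |
| 7% | 27.9% vs 37.2% | 9.3 points | 80.1% |
| 10% | 27.0% vs 36.0% | 9.0 points | 78.2% |
| 14.5% | 25.7% vs 34.2% | 8.6 points | 75.1% |

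The last row is a stacked worst case: all 10% of dropouts untraced, plus 5% of the remaining 90% unresolved (10% + 4.5%).

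**5. What 80% power would take at d = 10%.** The formula in step 1 with 27% vs 36% gives 417, and 417 × 1.70 = 709 per arm. At 684 per arm, power is 78.6%, so correcting the formula does not deal with the failure rule.

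**6. Sensitivity to where the extra children come from.** The table keeps 15 per cluster. If the added 10% came from the same 41 clusters (16.5 each, design effect 1 + 15.5 × 0.05 = 1.775), power would be 79.6% at d = 5% and 76.4% at d = 10%. The article does not say which is meant.

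**The case against.** A reader might infer that 677 per arm fails to deliver 80% power. The document does not establish that, for three reasons.

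- **The formula slip does not do it.** The figure of 615 contains slack from rounding up to whole clusters. The 609 children left after 10% loss still exceed the 605 needed, and power is 80.3%.
- **Dropout is not the same as unresolved.** The article plans to interview families who leave, to look into missing cards with the family and the vaccine clinic, and to exclude families who expect to stay less than 20 weeks. Only children still unclear after that count as failures. At 15 per cluster, power stays at or above 80% until about 7% are unresolved.
- **The meaning of 30% and 40% is open.** If they already count unresolved children as failures, there is no dilution and 677 per arm gives 84.2%.

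All three points stand, and they make the shortfall conditional. They do not remove the mismatch. If 30% and 40% are rates among children with known status, the power calculation omits the dilution. If they already include failures, a 10% allowance for dropout has no purpose under this analysis. On either reading the two sections need reconciling.

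The 75% figure should not be read as the expected power, because it needs every leaver untraced and ascertainment at the very edge of the stated expectation. The Bonferroni correction planned under Analysis of Quantitative Data lowers power further, but that is a separate matter and is kept out of these figures.

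**Conclusion.** The concern holds in a limited form. The dropout allowance does not match the rule that scores unknown status as failure. The arithmetic slip (677 in place of 684) is real but minor. The mismatch costs more: if the full planned 10% end up unresolved, power at 677 per arm is about 78%, not 80%, and the margin above 80% is used up at about 7%. The range is about 84% with none unresolved to 75% in the worst case.

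These figures rest on two-sided alpha of .05 without multiplicity adjustment, a design effect of 1.70, equal unresolved shares in the arms compared, and 30% and 40% being rates among children with known status. The document fixes neither the last of these nor the share left unresolved after tracing.

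**What to change.** - Correct the inflation to 615/0.90 = 684 per arm (3420 in total), in both the text and the Table 3 caption. This figure applies only if lost children leave the denominator.
- State the share of children expected to remain unresolved after tracing, and whether 30% and 40% already count them as failures.
- If they do not, restate power on the diluted rates for the number actually enrolled. At 677 per arm this is about 78% if the full 10% are unresolved, and about 81% at 5%.
- If they do, say so, and drop or explain the 10% allowance.

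The cost is one corrected figure and a few sentences, with a slightly less favourable power statement. Enrolment is reported as complete, and no added recruitment is needed.
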